## 5.2.7 Dose-Escalation Decisions

### 5.2.7.1 Dose-Escalation

Dose-escalation of MP0317 will be guided by a BLRM based on any DLTs observed during the DLT evaluation period as defined in Section 5.2.6. The BLRM is a well-established method to estimate the RDE/MTD in cancer patients. The adaptive BLRM will be guided by the Escalation With Overdose Control (EWOC) principle to control the risk of DLT in patients at escalated dose levels. This method allows the incorporation of available information and updates the model parameters based upon new data for any DLTs observed during the course of the study. The model's estimation of the probability of DLT and the recommendation of the next dose level will be performed at each escalation step and will utilize the entire history of all available data from previous cohorts. The model will be utilized to help decision-making by the DERC (Section 8.5).

Once the starting dose level of MP0317 is determined to be safe, it will be escalated per the provisional dose levels outlined in Table 3. Dose level -1 represents a dose that may be evaluated if dose level 1 is poorly tolerated. No dose de-escalation below this level is planned. If dose level -1 is poorly tolerated, the study will be terminated.

For the purposes of dose-escalation decisions, the first two cohorts will consist of 1 to 3 evaluable patients to assess safety and tolerability of the MP0317 starting dose. Based on the safety profile, additional patients may be included in these cohorts as needed. Each subsequent cohort will consist of 3 to 6 evaluable patients (Table 3). Dose-escalation decisions will be made once the cohort of

patients has met the criteria defined in Section 5.2.6. If only two patients in a cohort are evaluable and neither experiences treatment-related AEs  $\geq$  Grade 2 (NCI CTCAE v5.0), dose-escalation decisions may be considered. Q1w dosing schedule will be independent from q3w dosing schedule decision rules.

Based on the recommendation of the BLRM considering the highest dose that may not be exceeded at any decision point during escalation and the maximum dose increase allowed by the protocol, the DERC may advise exploration of an alternative dosing schedule (e.g. q1w) based on review of available clinical data. If a new schedule is explored the total planned dose intensity/exposure for the treatment cycle will not exceed that of a previously tolerated schedule, or a currently allowed escalation thereof, and the maximum daily dose will not exceed a 233% increase of a previously tolerated dose on any schedule. Additional higher and/or intermediate dose levels might be added to either schedule during the course of the study. Cohorts may be added at any dose level below the MTD to better understand the safety, PK and/or pharmacodynamic profile. Multiple dose levels below the MTD may be evaluated simultaneously to obtain PK and pharmacodynamic data across a range of doses and to establish the RDE/MTD.

There will be no intra-patient dose-escalation during the DLT evaluation period. However, after selection of the RDE, patients treated at a lower dose can be given the option to increase their dose to the RDE at the discretion of the Investigator and after consultation with the Sponsor.

**Table 3. Provisional Dose Levels for Dose-Escalation given Q3W or Q1W**

| Cohort Number   | Dose Level (mg/kg) | Dose schedule    | Number of Patients | Dose Level Increment (cumulative dose in mg/kg) |
|-----------------|--------------------|------------------|--------------------|-------------------------------------------------|
| -1 a | 0.01               | q3w              | 1 to 3             | - 66%                                           |
| 1               | 0.03               | q3w              | 1 to 3             | Starting dose                                   |
| 2               | 0.10               | q3w              | 1 to 3             | 233%                                            |
| 3               | 0.30               | q3w              | 3 to 6             | 200%                                            |
| 4               | 1.00               | q3w              | 3 to 6             | 233%                                            |
| 4b              | 0.50               | q1w b | 3 to 6             | 50% compared to 4                               |
| 5               | 3.00               | q3w              | 3 to 6             | 200% compared to 4                              |
| 5b              | 1.50               | q1w b | 3 to 6             | 200% compared to 4b                             |
| 6               | 10.00              | q3w              | 3 to 6             | 233% compared to 5                              |
| 6b              | 5.00               | q1w b | 3 to 6             | 233% compared to 5b                             |

a Dose level -1 represents a dose that may be evaluated if dose level 1 is poorly tolerated. No dose de-escalation below this level is planned. If dose level -1 is poorly tolerated, the study will be terminated.

b Initiated after DERC recommendation on the advice of the sponsor.

### 5.2.7.2 MTD Definition

The MTD is defined as the highest dose of study drug where the posterior probability of the true DLT rate in the target interval [0.16 to 0.33] of the MTD is above 0.50 with less than 25% risk of the true DLT rate being above 33%, and at least 6 patients have been treated in a confirmatory cohort of patients for the duration of the DLT evaluation period (Section 5.2.6).

### 5.2.7.3 Estimation of the RDE/MTD

A two-parameter BLRM employing the EWOC principle will be used during the escalation part for selection of doses to investigate, and for estimation of the MTD. Estimation of the MTD will be based

on the estimation of the probability of DLT during the DLT evaluation period in patients in the dose-determining set (DDS; Section 9.3.2). If the MTD is not reached during the dose-escalation part, the DERC will recommend the appropriate dose level as described above. The MTD of different dosing schedules will be determined independent from each other.

At all dose-escalation decision time points, the adaptive BLRM permits alterations in the dose increments based on the observed toxicities.

In general, dose-escalation will not exceed a 3.33-fold increase from the current dose being studied.

Dose-escalation, in either schedule (q1w, q3w), may be terminated at any time based on emerging safety concerns without establishing the MTD.

Based on emerging PK data, a dose that is considered acceptably safe after safety evaluation of the initial 3-6 patients (i.e. shown to be lower than any potential MTD) may be further expanded to better characterize the safety, PK and pharmacodynamic biomarkers at this dose level. Patients in the safety expansion part who do not have at least one post-screening efficacy assessment will be replaced.

### 5.2.8 Safety Waiting Period

The first doses between the first 2 patients in any cohort must be separated by a minimum of 7 days. No further safety waiting periods for patients on the same dose level are required, however, the DERC can increase the initial safety waiting period according to the nature of emerging safety data.

### 5.2.9 Treatment Modification (Delay, Interruption)

Guidelines for study treatment modifications are shown in Table 4.

The following should be taken into consideration:

- If supportive care is ineffective, drug administration delays or infusion interruptions should be considered to prevent worsening of the related AE(s).
- Drug administration delays or infusion interruptions may be implemented for Grade 1 related AEs if the Investigator feels it is in the interests of the patient's safety.
- Drug administration delay for any reason is allowed for up to 3 weeks. Re-starting treatment after a delay longer than 3 weeks may be allowed with approval of the Sponsor. During such delay, a limited set of study assessments/visits may be performed as determined by the Investigator in consultation with the Sponsor.
- Guidelines for the management of IRRs and CRS are provided in Appendix 12.6 and Appendix 12.7, respectively.
- Any treatment modifications such as drug administration delays or infusion interruptions should be entered in the eCRF.

Study treatment should be permanently discontinued for Grade 4 or recurrent Grade 3 AEs, unless otherwise specified in Table 4.

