### 5.2 Study Treatment Schedule and Administration

#### 5.2.1 Study Drug Dose

For each patient, the assigned dose of MP0317 will be based on the available cohort as recommended by the DERC. For the dose-escalation study part on a q3w schedule, the starting dose is 0.03 mg/kg q3w and up to 6 q3w dose levels are planned, as shown in Table 3. The doses to be evaluated on a q1w schedule in the dose-escalation part are shown in Table 3. A treatment cycle will be 3 weeks (21 days), with DLT evaluation period of 4 weeks after first study drug administration. See Section 5.2.9 for study treatment modifications.

[figure not shown]The table content is completely redacted with black boxes.

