## 5.2.6 Dose-Limiting Toxicity Evaluability

The evaluability rules for DLT assessment apply to dose-escalation cohorts only.

The DLT evaluation period is defined as the 4-week period after first study drug administration.

Patients evaluable for DLT must either a) receive at least 2 administrations of MP0317 at q3w dosing schedule or 3 administrations at q1w dosing schedule at the assigned dose level and be observed until pre-dose of Cycle 2 Day 8 or b) experience a DLT as defined in Section 5.2.5 during the DLT evaluation period.

A patient will not be considered as DLT evaluable and may be replaced if they experience any of the following events during the DLT evaluation period:

- Received an MP0317 dose which is less than 90% or more than 110% of the planned infusion dose.
- Discontinued from treatment due to AE or death unrelated to study treatment, withdrawal of consent, lost to follow-up or Investigator decision (unrelated to study treatment).

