## 5.2.10 Time Windows for Administration of Study Treatment

If the study treatment cannot be administered on the scheduled day for reasons other than AE the following time windows are allowed for q3w dosing schedule (Table 5) and q1w dosing schedule (Table 6):

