**Table 5. Time Windows for Administration of Study Treatment (Q3W)**

| Treatment Cycles                   | Allowed Time Window |
|------------------------------------|---------------------|
| For Dose-Escalation Cohorts |                     |
| Between Cycle 1 and 2              | 21 + maximum 2 days |
| From Cycle 2 to Cycle 4            | 21 $\pm$ 2 days     |
| From Cycle 5 onwards               | 21 $\pm$ 3 days     |
| For Safety Expansion Cohort |                     |
| From Cycle 1 to Cycle 4            | 21 $\pm$ 2 days     |
| From Cycle 5 onwards               | 21 $\pm$ 3 days     |

CONFIDENTIAL

May not be used, divulged, published, or otherwise disclosed without the consent of  
Molecular Partners AG, Schlieren, Switzerland

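### Sections 5.2.9 and 5.2.10 set conflicting limits on non-AE dose delays, and the DLT evaluability rule lets a q3w patient whose second dose falls after the 4-week window count as DLT-free

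*Protocol*

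**What the plan says.** **Delay limits.** Section 5.2.9 says "Drug administration delay for any reason is allowed for up to 3 weeks"; a longer delay needs Sponsor approval before treatment restarts. Section 5.2.10 then says "If the study treatment cannot be administered on the scheduled day for reasons other than AE the following time windows are allowed". For dose-escalation cohorts, Table 5 gives "21 + maximum 2 days" between q3w Cycles 1 and 2, and Table 6 allows at most 1 extra day on q1w during the DLT evaluation period. Neither section refers to the other.

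**DLT window.** Section 5.2.6: "The DLT evaluation period is defined as the 4-week period after first study drug administration". Section 5.2.5 counts a toxicity as a DLT only if it occurs within that period.

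**Evaluability.** Limb (a) of Section 5.2.6 sets this dosing condition: "receive at least 2 administrations of MP0317 at q3w dosing schedule or 3 administrations at q1w dosing schedule at the assigned dose level". Its second condition concerns follow-up, which has to last to just before the Day 8 visit of Cycle 2. The reference to the DLT evaluation period is attached only to limb (b), the patient who has a DLT. The events that make a patient non-evaluable are a dose outside 90% to 110% of plan and certain discontinuations; a late dose is not listed. The synopsis definition of the DDS has the same structure, and Section 9.3.2 sends the DDS to the Bayesian logistic regression model (BLRM).

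**The concern.** There are two linked problems.

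1. A site facing, say, a 10-day logistic delay to the second q3w dose finds it permitted in Section 5.2.9 and outside the window in Table 5. The text gives no way to choose.
2. The evaluability rule does not absorb the difference. Cycle 2 Day 8 moves with the delay, while the DLT window stays fixed to the first dose. With a long enough delay the patient satisfies limb (a) to the letter, yet the second dose and everything after it lie outside the period in which a DLT can be recorded. That patient enters the model as a non-event on the same footing as one observed after two doses.

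At stake is the DLT rate that drives overdose control in a first-in-human escalation. The error, where it occurs, runs towards a lower estimated rate.

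**Working it through.** **Inputs.** Cycle of 21 days and DLT period of 28 days from first dose (Section 5.2.1: "A treatment cycle will be 3 weeks (21 days), with DLT evaluation period of 4 weeks after first study drug administration"); delay limits from Section 5.2.9 and Table 5; prior from Table 23 (means -2.685 and -0.594, SDs 2 and 0.5, correlation 0); overdose limit of 25% from Section 9.4.1.1.

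**Step 1: day arithmetic for q3w.** Let *d* be the delay in days, with the first dose on Day 1.

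- Second dose: Day 1 + 21 + *d* = Day 22 + *d*
- Cycle 2 Day 8: Day 29 + *d*
- Post-dose-2 time inside the window: max(0, 28 - (21 + *d*)) = max(0, 7 - *d*) days

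At *d* = 0, Cycle 2 Day 8 is 28 days after the first dose. This reproduces the protocol's own equation of the two in Section 6.5.

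| Delay *d* | Second dose | Cycle 2 Day 8 | Post-dose-2 days in window |
|---|---|---|---|
| 0 | Day 22 | Day 29 | 7 |
| 2 (Table 5 limit) | Day 24 | Day 31 | 5 |
| 6 | Day 28 | Day 35 | 1 |
| 7 | Day 29 | Day 36 | 0 (boundary) |
| 8 | Day 30 | Day 37 | 0 |
| 14 | Day 36 | Day 43 | 0 |
| 21 (Section 5.2.9 limit) | Day 43 | Day 50 | 0 |

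Delays of 8 to 21 days put the second dose wholly after the window. Limb (a) is still met once the patient reaches the shifted Cycle 2 Day 8.

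**Step 2: does Table 5 close the gap?** Only for non-AE reasons, and only if it prevails over Section 5.2.9. A delay caused by a drug-related AE is outside Table 5, and Section 5.2.5 makes such a delay a DLT only when it exceeds 14 days. If the AE is not itself a DLT, a delay of 8 to 14 days gives the same result.

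**Step 3: possible effect on the model.** The BLRM was integrated on a grid with the Table 23 prior.

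- Check against Table 24: prior P(overdose) at 1.00 mg/kg is 0.162 (stated 0.166), and at 3.00 mg/kg 0.263 (stated 0.267).
- Check against Table 30, Setting 4a, Scenario 5 (0/3 at each of 0.03, 0.10, 0.30 and 1.00 mg/kg, 1/6 at 3.00): P(overdose) at 10 mg/kg is 0.242 (stated 0.244).
- Same data with one DLT-free patient removed at 3.00 mg/kg (1/5): P(overdose) at 10 mg/kg is 0.283.

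So 0.242 is below the 25% limit and 0.283 is above it. Five evaluable patients lie within the 3 to 6 that Table 3 gives for this cohort, so both data sets can arise at a decision.

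**The case against.** **A reconciling reading exists.** Section 5.2.10 can be taken as the specific rule, since its tables have rows for escalation cohorts in exactly this period. Section 5.2.9 would then be the outer limit before Sponsor approval is needed. Limb (a) directly follows the sentence defining the DLT period, so one may read the two doses as falling within it. This is plausible, but the text does not say it, and it leaves AE-related delays of 8 to 14 days untouched.

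**The loss is partial.** A late-dosed patient is still observed for the whole first cycle and all 28 days. What is missing is at most the week after the second dose. This stands, and it limits the size.

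**Replacement can undo the illustration.** If the late-dosed patient is replaced by a DLT-free one, 1/5 becomes 1/6 again. This stands too, although replacement is not compulsory once the minimum number of evaluable patients is reached.

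**Later toxicity is not hidden.** The dose-escalation review committee (DERC) considers all available safety data, including AEs that are not DLTs, and the model only guides its recommendation. This stands.

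**Stronger readings the documents do not support.**

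- A reader might infer that the same flip occurs at 0.30 mg/kg by comparing 1/3 with 1/2. Sections 5.2.7.1 and 9.2.2 require three evaluable patients from cohort 3 on. The two-patient exception needs no treatment-related AE of Grade 2 or above, so 1/2 is normally not a decision state.
- A reader might turn the share of permitted delay days beyond the window into a risk. That counts calendar days; the protocol gives no frequency of delays.

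**Conclusion.** Both parts hold on the text. Sections 5.2.9 and 5.2.10 contradict each other for non-AE delays, on q3w between Cycles 1 and 2 and on q1w during the DLT period. Independently, limb (a) and the synopsis DDS definition let a q3w patient delayed by 8 to 21 days count as DLT-free with no post-dose-2 observation in the window, against 5 to 7 days for a patient dosed within Table 5. A toxicity after that second dose cannot count as a DLT.

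The consequence is a possible downward bias in the modelled DLT rate, not a demonstrated wrong escalation. The 0.242 against 0.283 comparison assumes one late-dosed patient, no DLTs at lower doses and no replacement. How often such delays occur is unknown, and the DERC's wider review is a further safeguard. The evaluability consequence has been worked through for q3w only; none is claimed for q1w.

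**What to change.** 1. Reconcile Section 5.2.9 with Section 5.2.10 so that one limit governs non-AE delays during the DLT evaluation period, and state which section prevails. Which limit applies is for the sponsor to decide.
2. Align Section 5.2.6(a) and the synopsis DDS definition with the 4-week window: a DLT-free patient is evaluable only if the required administrations (2 on q3w, 3 on q1w) fall within the DLT evaluation period. Otherwise the patient is non-evaluable and is replaced under the existing rule. This also covers AE-related delays.

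The change is to wording in Sections 5.2.6, 5.2.9 and 5.2.10 and the synopsis. The downside is an occasional replacement patient. The rule does not equalise follow-up completely: a second q3w dose on Day 28 would still qualify with 1 day of observation left in the window.

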### 5.2.5 Dose-Limiting Toxicities

DLT evaluation and a recommendation regarding dose-escalation steps will be made by the DERC (Section 8.5), after consideration of all available safety information.

A DLT is defined as an AE or abnormal laboratory result meeting any of the criteria below, that is assessed by the Investigator as related to study treatment, and that occurs within the DLT evaluation period, including death (Section 5.2.6). Severity of all AEs will be assessed according to NCI CTCAE v5.0.

- Any  $\geq$  Grade 3 study drug-related non-hematologic AE, including the following abnormal laboratory results: Hepatic laboratory parameters potentially fulfilling Hy's Law criteria: AST or ALT  $\geq 3 \times$  ULN and concomitant total bilirubin  $\geq 2 \times$  ULN
- Any Grade 4 study drug-related hematologic AE or abnormal laboratory result (hematologic or non-hematologic)
- Grade 3 neutropenia lasting  $> 7$  days despite adequate standard-of-care medication
- Grade 3 or 4 febrile neutropenia (fever  $\geq 38.5$  °C)
- Grade 3 anemia that cannot be adequately treated by blood transfusions
- Inability to administer the next dose due to a drug-related AE or delayed administration of the next dose due to a drug-related AE and/or abnormal laboratory result lasting  $> 14$  days despite adequate medication
- Any other AE/abnormal laboratory result which, in the view of the Investigator and/or Sponsor, is deemed clinically significant and considered a DLT

Note that the following AEs/abnormal laboratory results, some of which are expected with the study treatment, will not be considered a DLT:

- Any transient Grade 3 or 4 abnormal laboratory results without any related clinical symptoms and lasting  $< 72$  h
- Grade 3 events that have not been optimally treated with standard-of-care medication, lasting  $< 7$  days
- Grade 4 amylase or lipase not associated with symptoms or clinical manifestations or radiologic signs of pancreatitis

- Grade  $\geq 3$  lymphocytopenia not associated with symptoms or clinical manifestations
- Grade 3 hypertension resolving within 48 h
- Grade 3 IRR resolving under adequate treatment (first event only)
- Grade 3 fatigue lasting  $\leq 14$  days

An AE considered by the Investigator to be disease-related should not be considered a DLT.

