| Non-infectious pneumonitis            | Grade 2                                                                                                                                                                                          | Withhold until recovered to Grade 0 to 1 a                                                                                                                                                                                                                                                                                                                                                                                               |
|                                       | Grade 3 or 4 or recurrent Grade 2                                                                                                                                                                | Permanently discontinue                                                                                                                                                                                                                                                                                                                                                                                                                             |
| Non-infectious colitis                | Grade 2 or 3                                                                                                                                                                                     | Withhold until recovered to Grade 0 to 1 a                                                                                                                                                                                                                                                                                                                                                                                               |

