| Endocrinopathies                      | Symptomatic hypophysitis
Diabetes mellitus type 1 associated with ≥ Grade 3 hyperglycemia (glucose > 250 mg/dL or > 13.9 mmol/L) or associated with ketoacidosis
Hyperthyroidism ≥ Grade 3 | Withhold until recovered to Grade 0 to 1 a
For patients with Grade 3 or 4 endocrinopathy that improved to Grade 2 or lower and is controlled with hormone replacement, if indicated, continuation of study treatment may be considered after corticosteroid taper, if needed. Otherwise treatment should be permanently discontinued.
Hypothyroidism may be managed with replacement therapy without study treatment interruption. |
| Non-infectious hepatitis              | Grade 2 with AST or ALT ≥ 3 to 5 x ULN or total bilirubin > 1.5 to 3 x ULN                                                                                                                       | Withhold until recovered to Grade 0 to 1 a                                                                                                                                                                                                                                                                                                                                                                                               |
|                                       | ≥ Grade 3 with AST or ALT > 5 x ULN or total bilirubin > 3 x ULN                                                                                                                                 | Permanently discontinue                                                                                                                                                                                                                                                                                                                                                                                                                             |

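### For a limited set of drug-related events, the DLT exemptions, the permanent-stop rules and the evaluability rules conflict, so a patient stopped early for toxicity may count as a DLT or drop out of the dose-determining set

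*Protocol*

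**What the plan says.** Four parts of the protocol bear on the same patient.

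- **Exemptions (Section 5.2.5).** Listed events are declared not to be DLTs. They include "Any transient Grade 3 or 4 abnormal laboratory results without any related clinical symptoms and lasting" under 72 h; "Grade 4 amylase or lipase not associated with symptoms or clinical manifestations or radiologic signs of pancreatitis"; asymptomatic lymphocytopenia of Grade 3 or higher; and "Grade 3 events that have not been optimally treated with standard-of-care medication, lasting" under 7 days.
- **DLT criteria (Section 5.2.5).** One criterion is "Inability to administer the next dose due to a drug-related AE". The section does not say whether this or the exemption list prevails.
- **Stopping treatment (Section 5.2.9 and Table 4).** "Study treatment should be permanently discontinued for Grade 4 or recurrent Grade 3 AEs, unless otherwise specified in Table 4". Table 4 has no row for amylase, lipase or lymphocytopenia. It lists a permanent stop for pneumonitis at "Grade 3 or 4 or recurrent Grade 2", for hepatitis from "Grade 3 with AST or ALT > 5 x ULN or total bilirubin > 3 x ULN", and for nephritis from a first Grade 3.
- **Evaluability (Sections 5.2.6 and 9.3.2).** There are two routes to being evaluable. Route (a) asks that the patient "receive at least 2 administrations of MP0317 at q3w dosing schedule or 3 administrations at q1w dosing schedule at the assigned dose level", with observation lasting to pre-dose on Cycle 2 Day 8. Route (b) is to have a DLT. A patient meeting neither is outside the dose-determining set and is replaced if needed. The only AE-related ground on the replacement list of Section 5.2.6 is an AE or death unrelated to treatment. A stop for a related but exempt AE is not addressed there.

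**The concern.** For some events the exemption list says no DLT, Section 5.2.9 or Table 4 says treatment should stop for good, and the stop itself meets a DLT criterion.

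Take a related Grade 3 pneumonitis in Cycle 1 on the q3w schedule that was not optimally treated and lasted 5 days. Under the inability-to-dose criterion it is a DLT. Under the exemption it is not. The patient has then had one infusion, fails both routes of Section 5.2.6, and can be replaced.

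The dose-determining set alone feeds the BLRM and the MTD estimate. If the exemption prevails, patients taken off drug for related toxicity can leave that set and tolerant patients can take their place. That selection favours escalation. DLT incidence is a primary endpoint of this first-in-human trial, and the protocol's background names hepatotoxicity among the dose-limiting effects of earlier CD40 agonists.

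**Working it through.** **Step 1: which exempt events collide with a stop rule.**

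| Exempt event (5.2.5) | Stop under 5.2.9 or Table 4? |
|---|---|
| Asymptomatic laboratory result under 72 h | Grade 4, or recurrent Grade 3, if recorded as an AE |
| Asymptomatic Grade 4 amylase or lipase | Yes, if recorded as an AE |
| Asymptomatic lymphocytopenia, Grade 3 or higher | Grade 4, or recurrent Grade 3, if recorded as an AE |
| Grade 3 event not optimally treated, under 7 days | At first occurrence for pneumonitis, nephritis or hepatitis; for most others, only if it recurs |
| Grade 3 hypertension within 48 h; Grade 3 fatigue up to 14 days | Only if it recurs |
| First Grade 3 infusion reaction | No |

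**Step 2: what happens to the patient.** The q3w minimum is 2 doses, the second due on Day 22. The q1w minimum is 3 doses, the third due on Day 15.

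- Stopped before the minimum: a DLT (in the set by route b), or not a DLT (fails both routes and leaves the set).
- Stopped after the minimum and observed to pre-dose on Cycle 2 Day 8: a DLT or a counted non-DLT.

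**Step 3: what one patient's coding does to the model.** Inputs:

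- Model (Section 9.4.1.2): logit p(d) = log(α) + β·log(d / 1 mg/kg).
- Prior (Table 23): (log α, log β) normal with means −2.685 and −0.594, SDs 2 and 0.5, correlation 0.
- Overdose: p(d) ≥ 0.33. A dose is barred if the posterior probability of overdose exceeds 0.25 (Section 9.4.1.1).
- Data: 0/3 at every lower dose; at the current dose 1/3 (DLT), 0/3 (non-DLT, or removed and replaced by a tolerant patient) or 0/2 (removed, not replaced).

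The posterior was integrated numerically on a grid. P(overdose) at the next dose:

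| Current → next (mg/kg) | 1/3: Table 30 | 1/3: re-run | 0/3: Table 30 | 0/3: re-run | 0/2: re-run |
|---|---|---|---|---|---|
| 0.03 → 0.10 | 0.261 | 0.253 | 0.014 | 0.015 | 0.022 |
| 0.10 → 0.30 | 0.193 | 0.190 | 0.016 | 0.016 | 0.021 |
| 0.30 → 1.00 | 0.241 | 0.237 | 0.032 | 0.031 | 0.039 |
| 1.00 → 3.00 | 0.306 | 0.303 | 0.055 | 0.053 | 0.066 |
| 3.00 → 10.00 | 0.384 | 0.389 | 0.084 | 0.085 | 0.105 |

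The re-run agrees with these Table 30 entries to within 0.008. (In the 0.30 mg/kg row of Setting 1, Table 30 prints both 0.063 and 0.032 for the same quantity; the re-run supports 0.032.)

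Against 0.25, the DLT coding bars the next dose at 0.03, 1.00 and 3.00 mg/kg, by a thin margin at 0.03. The other codings allow it everywhere. At 0.10 and 0.30 mg/kg all codings allow it.

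**Step 4: how long the bar lasts.** Table 30, Setting 4a, adds three patients without a DLT at the same dose, giving 1/6. P(overdose) at the next dose is then 0.116, 0.180 and 0.244 for current doses 0.03, 1.00 and 3.00 mg/kg (re-run 0.111, 0.180, 0.242). Escalation is allowed again. The disputed coding therefore decides whether the current dose is expanded before escalation.

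**Step 5: keeping the patient in the set is not enough.** At 1.00 mg/kg, entering a one-infusion patient as a non-DLT gives 0.053 at 3.00 mg/kg. That is lower than dropping the patient (0.066) and equal to replacing the patient with a tolerant one.

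**The case against.** The strongest reply is that a coherent reading exists. Section 5.2.9 speaks of what should be done, under a table of guidelines, and applies to AEs. Under Section 8.1.2 a laboratory value that does not meet the AE definition is not reported as one, so a brief, harmless Grade 4 value need not trigger a stop. The replacement list names only unrelated AEs, so a related AE that ends treatment can be read as a DLT through the inability criterion. A catch-all criterion also lets the Investigator or Sponsor declare a DLT.

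Part of this stands. It confines the laboratory cases to results recorded as AEs, and it rules out the inference that harmless laboratory findings generally become DLTs. It does not settle the matter. Section 8.1.2 also makes a result an AE when the protocol requires a treatment change, which is circular here. Grade 3 pneumonitis does not depend on that section at all. The catch-all is discretionary, and the exemption note that follows it says the listed events are not DLTs.

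The second reply is that the DERC sees all safety data, including AEs that are not DLTs, and that the Sponsor decides. That is correct and softens the consequence. It does not correct the counts behind the overdose limit and the MTD estimate. The rule in Section 5.2.7.1 that lets escalation be considered with two evaluable patients looks only at the AEs of those two, so a removed patient's event does not count there.

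**Conclusion.** The conflict is real for the events in Step 1, and no stated rule resolves it. If the exemption prevails, the rules as written remove some related, treatment-ending toxicity from the data that drive escalation. If the inability criterion prevails, the exemption has no effect for these events.

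Three stronger inferences are tempting, and the documents do not support them:

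- That every exempt event leads to a mandatory stop. A first Grade 3 infusion reaction and a single short episode of Grade 3 hypertension or fatigue trigger none, and the wording is advisory.
- That one patient could be a DLT, a counted non-DLT or replaced. The options depend on timing, as Step 2 shows.
- That one patient's status always decides the next cohort. It crosses the limit at three of the five current doses examined, and the model advises the DERC rather than deciding.

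The figures assume cohorts of 3, clean lower cohorts and the q3w prior. The q1w prior is still to be derived, so no size is claimed for that schedule. Section 6.3 records that the first two q3w cohorts had been reviewed before this version, so the 1.00 and 3.00 mg/kg rows matter most for what lies ahead.

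This should be fixed. It is a gap in precedence for uncommon combinations of events, and it does not undermine the design as a whole.

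**What to change.** Reconcile Sections 5.2.5, 5.2.6, 5.2.9 with Table 4, and 9.3.2 so that each event in Step 1 has exactly one status. Which clinical rule gives way is for the sponsor to decide.

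The reconciled text should meet two conditions for a patient permanently discontinued in the DLT window for a study-drug-related event:

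1. The patient is not removed from the dose-determining set and replaced.
2. The patient is not entered as a tolerated non-DLT without the minimum exposure of Section 5.2.6 a).

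Until this is done, any such patient should be reported to the DERC individually, with the BLRM result under each possible coding.

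The cost is a few sentences in the protocol, with matching text in the DERC charter. The downside is that DLT counts may become slightly less favourable, and a dose may need expanding before escalation.
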